## Abstract

**Background:**

Patients with heart failure with preserved ejection fraction (HFpEF) have a low functional status, which in turn is a risk factor for hospital admission and an important predictor of survival in HFpEF. HFpFE is a heterogeneous syndrome and recent studies have suggested an important role for careful, pathophysiological-based phenotyping to improve patient characterization. Cardiac rehabilitation has proven to be a useful tool in the framework of secondary prevention in patients with HFpEF. Facilitating decision-making and implementing cardiac rehabilitation programs is a challenge in public health systems for HFpEF management. The FUNNEL + study proposes to evaluate the efficacy of an exercise and education-based cardiac rehabilitation program on biomechanical, physiological, and imaging biomarkers in patients with HFpEF.

**Discussion:**

Identifying objective functional parameters indicative of HFpEF and the subsequent development of functional level stratification based on functional impairment ("biomechanical phenotypes") may help clinicians identify cardiac rehabilitation responders and non-responders and make future clinical decisions. In this way, future pharmacological and non-pharmacological interventions, such as exercise, could be improved and tailored to improve quality of life and prognosis and reducing patients' hospital readmissions, thereby reducing healthcare costs.

**Trial registration:**

NCT05393362 (Clinicaltrials.gov).

**Supplementary Information:**

The online version contains supplementary material available at 10.1186/s12872-023-03555-7.

## Background

Cardiovascular diseases continued to be the principal cause of disability-adjusted life years (DALYs) due to non-communicable diseases (NCDs) and the leading cause of death, especially in countries with a higher sociodemographic index and longer life expectancy [1–3]. Within cardiovascular diseases, it has been estimated that heart failure (HF) has a prevalence of approximately 2% to 3%, arising in more than 23 million people worldwide [4, 5]. The incidence and prevalence of HF are increasing due to the ageing of the world population, with patients over 75 years of age having the highest risk of developing this condition [4, 6–8]. Within the complex entity of HF, three subtypes have been differentiated: HF with preserved ejection fraction (HFpEF), HF with mildly reduced ejection fraction (HFmrEF), and HF with reduced ejection fraction (HFrEF). These three diagnostic entities coexist in the population with HF, the most prevalent being HFpEF, with prevalence rates of 50%. HF constitutes the essential hospital diagnosis in older adults, being the leading cause of hospital admissions for people over 65 and contributing to the increase in healthcare costs in Western societies [4–6]. Functional status is a potentially modifiable risk factor for hospital admission and appears to be an important discriminator between the different HF subtypes [9].

HFpEF patients present distinctive functional characteristics, such as reduced aerobic capacity, decreased muscle strength in the lower extremities, low weekly physical activity, and exercise intolerance, accompanied by fatigue and dyspnoea symptoms [10–15]. These functional characteristics cause HF patients to show impaired functional abilities, experience impaired ability to perform activities of daily living, and suffer reduced quality of life [10, 12, 15]. Furthermore, it has been shown that patients with chronic HF present some changes in their gait pattern, with a lower gait speed than healthy subjects of the same age [16]. While gait speed is independently associated with survival, death, and hospitalisation in HF patients [8, 9, 17], maximal aerobic capacity has been inversely correlated with the severity of HF and directly related to prognosis and survival life expectancy [11, 12, 18, 19]. Similarly, lower extremity skeletal muscle mass and strength could predict long-term survival in patients with HF [12, 20].

When evaluating functional parameters in patients with HF, maximal oxygen consumption (VO_2_max) obtained from a cardiopulmonary exercise test (CPET) is considered the Gold Standard measure of cardiovascular functional capacity. Some functional tests have been used in clinical practice, such as the 6-min walk test (6MWT), which indirectly measures cardiovascular functional ability. Strength could also be assessed using the one repetition maximum (1RM) test, handgrip strength measurement (HGS), or the Short Physical Performance Battery (SPPB), as a valuable and indirect measure of this capacity [11]. Most geriatric populations present a high degree of fragility and dependence from the physical, cognitive, and psychological points of view, so their evaluation is essential [21]. SPPB and the Timed Up and Go (TUG) test have been established as practical clinical tests to assess frailty as a phenotype in HF patients [22–25].

By assessing the functional parameters used in the clinic, it has been possible to evaluate the effectiveness of Cardiac Rehabilitation (CR) in improving quality of life, functional capacity, exercise performance, and HF-related hospitalisations [26, 27]. CR is a multidimensional treatment designed to promote lifestyle changes and physical activity, optimise medical treatment, control risk factors, and address social and psychological problems following the development of heart disease [28]. CR programmes have a strong recommendation (Class 1A) in major HF practice guidelines, as it is considered a cost-effective intervention in HF, reducing recurrent hospitalisations and healthcare expenditure [7, 26, 29]. Benefits have also been shown on anthropometric, blood markers and physiological (VO_2_max) related outcomes, and cardiac imaging structural biomarkers such as ventricular ejection fraction [29–31].

Biomechanical biomarker assessment is possible through the parameterisation of human movement [32]. Inertial sensors have proven to be an accurate and reliable method for biomechanical human motion analysis and are used as a reference for validating motion capture instruments [32–35]. Currently, a good correlation between measurements obtained by inertial sensors and depth chambers has been demonstrated in the parameterisation of functional tests [34]. Biomechanical biomarkers could identify normal and pathological movements, the degree of impairment, the planning of rehabilitation strategies, and the evaluation of the effect of various interventions [32]. Therefore, it could be interesting to identify objective functional parameters affected in patients with HF, help stratify them based on different levels of functional impairment and identify those patients who are responders and non-responders to CR programmes. However, no biomechanical biomarkers have been assessed as an objective measure of the functionality of HF patients. Thus, the benefits of CR programmes on these biomechanical biomarkers have not been determined.

Facilitating decision-making and implementing CR programmes is a challenge in public health systems for HF management. This study proposes evaluating the efficacy of the CR programmes through a randomised clinical trial (RCT) on biomechanical, physiological, and imaging biomarkers in HF patients. In addition, it aims to validate the biomechanical analysis obtained using motion capture systems to assess objective functionality in elderly patients with HFpEF.

## Methods

### Trial design

This study protocol followed the SPIRIT 2013 Recommendations [36] during its development. More details are shown in Additional file 1. The present study shows the proposed two-arm crossover RCT comparing an exercise-based CR programme with education in patients with HF. Patients will be randomised into two groups by simple randomisation using a random number generator on the computer. The study design is shown in Fig. 1. The RCT is based on work within the Biomedical Research Institute of Malaga (IBIMA) between the Internal Medicine Unit and the Cardiology Unit of the Regional University Hospital of Malaga (HRUM), together with the support of the University of Malaga (Malaga, Spain). This project has been submitted to the Malaga Provincial Ethics Committee (2198-N-22).

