### Recruitment and inclusion

They will be patients over 70 years of age with a diagnosis of HFpEF, who are clinically stable, and who are being followed in this unit. A clinically stable patient is defined as a patient who has not been hospitalised for HF decompensation, has not undergone treatment modification, and has a stable NYHA grade 2–3 in the last 3 months. The diagnosis of HF and optimal treatment will be established according to Spanish and European HF clinical practice guidelines [29, 37]. Inclusion and exclusion criteria are detailed in Table 1.

**Table 1 Tab1:** Inclusion and exclusion criteria

*Inclusion criteria*	*Exclusion criteria*
Age 70 years or older	Cardiac pathologies that do not have HF status
Diagnosis of HFpEF followed in the unit Intention to change sedentary behaviours expressed by the subject	NYHA scale score 4
Clinical & haemodynamic stability	Have been hospitalised before three months or less
To Receive optimal medical treatment	MMSE score less than 24
	Inability to get up from a chair five times
	Unable to walk or independently without a walking aid (cane, crutch or walker)
	To participate in an experimental study where they receive treatment
	Lack of informed consent

*HF* Heart Failure, *MMSE* Mini-Mental State Examination, *NYHA* New York Heart Association

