### Sample size calculation

The sample size was calculated using G Power 3.1.9.2 software (University of Düsseldorf, Germany). Based on an expected difference in VO_2_max increase of 3.0/ml/kg/min in the intervention group and 0.6 ml/kg/min in the control group (based on the result of the EUCaRE Study, Prescott et al. 2020 PMID 32102550 [48]). Assuming a statistical power of 80% and an alpha error of 0.05, the required sample size is 55 patients per arm and carries a loss rate of 15%, and this would make a total of 126 (63 per arm).

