### Statistical analysis

Data sets will be processed using the Statistical Package for the Social Sciences (SPSS) for Windows (version 19.0, SPSS Inc., Chicago, IL, USA). Qualitative variables will be described by absolute and relative frequency (percentage). Quantitative variables shall be presented by the mean and standard deviation if the data follow a normal distribution or by the maximum, minimum, and three quartiles if the data do not follow such a distribution. The Shapiro–Wilk test will be used to analyse the normal distribution of the data (*p* > 0.05). The difference in means between the two groups will be obtained using Pearson's Chi-square test (× 2) for qualitative variables. To express the differences in means in the quantitative variables between the two groups, the bivariate analysis will be used using the parametric Student's t-test for independent samples in the case of normal data distribution, or the non-parametric Mann–Whitney U test, if there is no normal distribution of the data. The degree of statistical significance shall be set at a *p*-value < 0.05. 95% confidence intervals (CI) will be calculated for the mean differences between the study groups.

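### Simple randomisation leaves arm size and NYHA balance to chance, and the unadjusted tests named for the comparison do nothing to correct it

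*Protocol article*

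**What the plan says.** Trial design fixes the allocation method: "Patients will be randomised into two groups by simple randomisation using a random number generator on the computer". It mentions no blocks or strata.

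Sample size calculation states that "the required sample size is 55 patients per arm and carries a loss rate of 15"%, and that "this would make a total of 126 (63 per arm").

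Recruitment and inclusion requires that a patient "has a stable NYHA grade 2–3 in the last 3 months", so the sample mixes two functional classes. Class is known at eligibility. Study duration and timing places the baseline assessment before randomisation, so baseline VO2peak is known by then too.

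For quantitative outcomes, Statistical analysis names the "parametric Student's t-test for independent samples in the case of normal data distribution, or the non-parametric Mann–Whitney U test". It mentions no adjustment for baseline or for any prognostic factor.

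**The concern.** Two choices combine. Unrestricted allocation lets the arms differ by chance in size and in patient mix. The named tests then use none of the information collected before allocation.

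The article itself says that VO2peak reflects disease severity in heart failure. If one arm happened to contain clearly more NYHA 3 patients, readers would ask how much of an observed difference, or of its absence, came from that. An unadjusted test gives no answer. It also leaves variation that baseline data could explain in the error term, so the confidence interval is wider than it need be. What is at stake is precision and a result that is easy to read, not validity.

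**Working it through.** **Inputs from the article.** N = 126, planned as 63 per arm; 55 evaluable per arm; 15% loss; 80% power; alpha 0.05; difference 3.0 − 0.6 = 2.4 ml/kg/min.

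**Assumptions.** Two-sided test. The article states no SD, so 55 per arm cannot be reproduced, only solved backwards. A t-test with 55 per arm, a difference of 2.4 and 80% power implies SD = 4.45 (4.49 by the normal approximation). Every power figure below rests on this. The step from 55 to 63 does reproduce: 55 × 1.15 = 63.25.

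**Arm size.** One arm's size is Binomial(126, 0.5).
- SD = √126 / 2 = 5.6; central 95% range 52 to 74.
- P(exactly 63/63) = 7.1%.
- P(smaller arm has 57 or fewer) = 33%.

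**Power cost of unequal arms.** Noncentral t with noncentrality 2.4 / (4.45 × √(1/n1 + 1/n2)), each arm multiplied by 0.85 for loss.

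| Allocation | Power after 15% loss | Power with no loss |
|---|---|---|
| 63/63 | 78.9% | 85.1% |
| Simple randomisation, averaged over all splits | 78.6% | 84.8% |
| 52/74 | 77.7% | 84.0% |

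After loss, the cost is 78.9 − 78.6 = 0.3 points on average and 78.9 − 77.7 = 1.2 points at the edge of the 95% range.

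**Balance in a prognostic factor.** The split between NYHA 2 and 3 is not given; assume half and half.
- SE of the difference in proportions between arms = √(0.25 × 2/63) = 8.9 percentage points; 95% range about ±17 points.
- A difference of 10 points or more occurs in 26% of allocations.

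**What that does to the estimate.** If the classes differ by Δ in the analysed outcome, an imbalance of q shifts the estimate by qΔ. With q = 0.10 and an assumed Δ = 2, the shift is 0.2 ml/kg/min. The SE of the treatment difference after loss is 4.45 × √(2/53.55) = 0.86, and the target is 2.4.

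**Gain from adjusting for NYHA class.** A half-and-half factor explains 0.25Δ² of a variance of 4.452² = 19.82.
- Δ = 1: 0.25/19.82 = 1.3% explained; residual SD 4.452 × √0.987 = 4.42; power after loss 79.4%, a gain of 0.5 points.
- Δ = 3: 2.25/19.82 = 11.4% explained; residual SD 4.452 × √0.886 = 4.19; power after loss 83.5%, a gain of 4.6 points.

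**Gain from adjusting for baseline VO2peak.** With equal variances at baseline and follow-up and correlation ρ, the variance relative to a change score is (1 − ρ²) / (2(1 − ρ)) = (1 + ρ)/2.
- ρ = 0.5: 0.75, a 25% reduction.
- ρ = 0.8: 0.90, a 10% reduction.

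The article does not give ρ. The two gains overlap if class and baseline VO2peak are related, so they should not be added.

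**The case against.** **Simple randomisation is a valid method.** This stands. It is unbiased, the unadjusted test keeps its type I error, and chance imbalance is already reflected in the standard error. A reader might infer that the trial fails to deliver its stated arm sizes. It does not: 63 is the expected size under 1:1 allocation and a planning figure, and the two sections do not contradict each other.

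**The imbalance may barely touch the outcome.** This stands in part. A reader might infer that an imbalance in NYHA class enters the estimate in full. The sample size is built on the increase in VO2, whereas the article ties severity to its level. If changes are compared, a difference in level largely cancels, and nothing in the article shows that class predicts the change. The gain from adjusting for NYHA class is therefore given as a range over assumed values.

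**Arms short of 55 evaluable patients.** A reader might blame simple randomisation for this. The main cause is elsewhere: even equal arms of 63 leave 63 × 0.85 = 53.6, because 55 was multiplied by 1.15 and not divided by 0.85. That is a separate matter.

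**The crossover makes each patient their own control.** It could, under a within-patient analysis. The article names only independent-samples tests for comparing groups, so as written that protection is not used. A separate analysis plan, not shown, might add adjustment.

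**Blocking has a price.** This stands. Both interventions run in one hospital unit and patients are not blinded, so restricted allocation adds some predictability. Blocking alone would fix only arm size, where little is lost.

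**Conclusion.** The point holds as a minor one. The allocation method guarantees neither equal arms nor balance in NYHA class, and the named tests leave chance imbalance uncorrected. No bias follows. Unequal arms cost about 0.3 points of power on average and 1.2 points at 52/74, which would not by itself justify changing the allocation.

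The part worth acting on is the analysis. It ignores two variables that are known before randomisation, and using them would improve precision and remove the doubt raised by a visible imbalance. The size of the gain is uncertain. It rests on an SD of 4.45 solved from the article's own 55 per arm, a two-sided test, an even NYHA split, and assumed class differences and baseline correlations. The sample size is not invalidated by this point.

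**What to change.** **Main change, in Statistical analysis.** Replace the unadjusted comparison of VO2peak with a linear model for the follow-up value that contains treatment group, NYHA class (2 or 3) and baseline VO2peak. Report the adjusted difference with its 95% confidence interval as the primary result. This takes one or two sentences and no new data, and the software already named can fit the model. It should be fixed before any outcome data are examined by group.

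**Optional change, in Trial design.** Replace simple randomisation with a computer-generated list in permuted blocks of randomly varying size, stratified by NYHA class, with block sizes concealed from those who recruit and assess. The cost is a different list and slight predictability of the last allocations in a block in an open-label trial. If recruitment has begun under simple randomisation, the analysis change alone addresses the prognostic imbalance.

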**Fig. 1 Fig1:**
[figure not shown]
CONSORT Flow diagram; CR Cardiac Rehabilitation, HF Heart Failure, MMCSE Mini-Mental Cognitive Examination, NYHA New York Heart Association Classification

### Study duration and timing

Recruitment and eligibility assessment of participants from the Internal-Cardiac Unit will be performed first. Patients who meet the eligibility criteria and wish to participate in the study will be required to provide written informed consent to participate in the study. Once the informed consent is signed, study variables will be collected. After baseline assessment, patients will be randomised to the control (Education) or intervention (CR) group. The interventions will have an estimated duration of 3 months. Patients will be assessed right after the intervention (follow-up/analysis 1) and at six months (follow-up/analysis 2). This way, depending on the group allocation, the different intervention groups will be reassigned. Data collection is expected to be completed about 1 year after the beginning of the study. The timeline of the study is represented in Fig. 2.

**Fig. 2 Fig2:**
[figure not shown]
Study timetable; * Time distribution of the different phases within the study. The numbers assigned in the second row refer to the month from the start of the study in which the different phases of the study are planned to be carried out

### Recruitment and inclusion

They will be patients over 70 years of age with a diagnosis of HFpEF, who are clinically stable, and who are being followed in this unit. A clinically stable patient is defined as a patient who has not been hospitalised for HF decompensation, has not undergone treatment modification, and has a stable NYHA grade 2–3 in the last 3 months. The diagnosis of HF and optimal treatment will be established according to Spanish and European HF clinical practice guidelines [29, 37]. Inclusion and exclusion criteria are detailed in Table 1.

**Table 1 Tab1:** Inclusion and exclusion criteria

*Inclusion criteria*	*Exclusion criteria*
Age 70 years or older	Cardiac pathologies that do not have HF status
Diagnosis of HFpEF followed in the unit Intention to change sedentary behaviours expressed by the subject	NYHA scale score 4
Clinical & haemodynamic stability	Have been hospitalised before three months or less
To Receive optimal medical treatment	MMSE score less than 24
	Inability to get up from a chair five times
	Unable to walk or independently without a walking aid (cane, crutch or walker)
	To participate in an experimental study where they receive treatment
	Lack of informed consent

*HF* Heart Failure, *MMSE* Mini-Mental State Examination, *NYHA* New York Heart Association

## Interventions

Both the Education and CR interventions will take place in the internal medicine unit of the HRUM. Medical and nursing care will be available during Education and CR sessions to ensure the safety of participants Study collaborators will be instructed to record any incidents related to possible adverse events that may be associated with the interventions.

### Experimental group: CR program

The CR programme will consist of aerobic and strength exercise sessions. Exercises will be individualised after assessment of short (strength exercise) and long (aerobic exercise) efforts. They will be performed two days a week and at least 48 h between sessions. Progression will consider a clinical criterion, determined by the absence of HF symptoms at the current intensity, and a time criterion in which, as long as the clinical criterion is met, the intensity will be increased every two to three weeks. The progression in aerobic training intensity is established based on Skinner's three-phase model [38] and the recommendations of current European cardiac rehabilitation guidelines [29]. The structure of the standard session, the criteria for progression in both aerobic and strength training, the phases of training, the periodisation of the programme, and the monitoring variables in the session can be found in detail in Additional file 2.

In addition, embedded in the exercise intervention, education on healthy lifestyle habits will be needed. A series of competencies in healthy lifestyle habits relevant to the population with HF will be established, which will be evaluated using a questionnaire with an evaluation rubric format for each of the competencies. The competencies will be evaluated during the training sessions in an informal way. Depending on the results obtained, they will be reinforced by strengthening unconsolidated skills using specific educational material.

### Control group: Education

The control group will receive personalized educational embedded in the program for twelve weeks on HF complications, functional decline, and healthy lifestyle habits. The format of the sessions will be in the form of face-to-face or online master classes, depending on the availability of the participants, in which the active participation of both volunteers and their relatives/caregivers will be encouraged.

